Exercise progression is guided by symptomatic response, such that the participant is advised that on cessation of the exercise, the pain should remain no worse than pre-exercise [48]. Participants with more severe pain will start on a lighter regime, and this will be guided by the baseline functional assessment by the treating physiotherapist. Participants will be advised to exercise at a level they find acceptable and tolerable. Participants are able to start exercising, if they wish, at a very low level, with little or no short-term pain increase, and progress when they feel comfortable and confident. Regression will be in the form of reduced repetitions, or lightening the exercise, for example to double leg squats 0–30° knee flexion. Progression can be in the form of increased repetitions or increasing the load by moving to plyometric exercises, such as jumping and hopping, for participants with higher sporting requirements. The physiotherapist will plan the exercise, motivate and review participant’s physical performance and expectations [35].

A single exercise approach will be used for this intervention. Poor levels of exercise adherence are well documented [51], and it has been suggested that a single exercise represents a pragmatic time saving approach [52]. Additionally, as previously discussed, the optimal dosage of an exercise prescription is unknown, and a single exercise approach may allow better monitoring of dosage and adherence. Importantly, it will enable the participant to observe others (the physiotherapist) perform the task successfully, and facilitate the development of mastery of the task. This combined with specific verbal and social persuasion from the physiotherapist, will further promote reconceptualisation of the pain, specific to the participant and their context; all thought to be key modifiers of perceived self-efficacy [53].

The participants will be advised that the exercise should be performed twice a day. The participant will be encouraged to self-direct in progressing/regressing the repetitions, as guided by their pain response, thus further internalising the locus of control and moving towards self-management [53].

Goal setting will be a central part of the intervention. The reconceptualisation of pain through the exercise intervention leads to the reconceptualization of pain in the participant’s daily activities, including sport and leisure activity, and setting goals helps this transition.

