Self-efficacy has been shown to be a strong predictor of disability in patients with MSK pain [67]; therefore, the General Self Efficacy Scale will also be used (GSES) [68]. The GSES is a 10-item questionnaire with each question asking the degree with which the participant agrees with the statement, with a 4-point Likert scoring structure ranging from ‘not at all’ (1) to ‘exactly true’ (4). The questions are used to explore the participants’ perceived belief at coping with a range of stressful and challenging demands, with a total possible score of 10 to 40. The GSES has been shown to have high reliability and validity across multiple languages and settings [69].

Patients characteristically withdraw from participation in sport and leisure activities [6]; therefore, the number of times the participant has participated in leisure time sport or exercises within a week will be recorded.

The generic EQ-5D-5L is a generic health outcome used widely internationally [70]. The questionnaire has five questions about mobility, usual activities, self-care, pain and discomfort and anxiety and depression. The results are converted into in single summary index and can be used to aid and assist any future economic evaluation planned for the definitive RCT.

Compliance is the act of conforming and following the prescribed dosage, timing and frequency of the exercise. Feasibility outcomes of compliance levels will be monitored through a participant activity diary. Participants will be asked to complete an exercise diary daily for 6 months indicating how many repetitions they completed of their exercise.

Non-responders will be telephoned after 7 days to encourage them to complete the forms and return them.

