### Data collection methods

#### Phases 1 and 3

Interviews will be recorded with a digital recorder. The interviews will then be transcribed verbatim and analysed.

#### Phase 2

Baseline data will be captured prior to randomisation in the physiotherapy clinic. Follow-up assessments will be 3 and 6 months (by post with a stamped addressed envelope for return). Participants will be asked to post back their exercises diary at the 6-month follow-up.

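### The exercise diary as described covers only part of the plan's own definition of compliance, and its single return at 6 months risks selectively missing adherence data

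*Protocol article*

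**What the plan says.** All references are to the protocol article.

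- Outcome assessments gives the definition: "Compliance is the act of conforming and following the prescribed dosage, timing and frequency of the exercise". It then names the instrument: "Feasibility outcomes of compliance levels will be monitored through a participant activity diary". The content follows: "Participants will be asked to complete an exercise diary daily for 6 months indicating how many repetitions they completed of their exercise". The same section has non-responders telephoned after 7 days to encourage return of forms.
- Exercise intervention sets the frequency: "The participants will be advised that the exercise should be performed twice a day". The number of repetitions is not fixed: "The participant will be encouraged to self-direct in progressing/regressing the repetitions, as guided by their pain response". Load can change separately: "Progression can be in the form of increased repetitions or increasing the load by moving to plyometric exercises". Regression may likewise be by fewer repetitions or by a lighter exercise. The section offers better monitoring of dose and adherence as one reason for using a single exercise.
- Data collection methods, Phase 2, gives two postal contacts: "Follow-up assessments will be 3 and 6 months (by post with a stamped addressed envelope for return". On the diary it says: "Participants will be asked to post back their exercises diary at the 6-month follow-up". No diary return is described at 3 months.
- Planned data analysis, Phase 2, rules out imputation and sets 75% thresholds for recruitment and for reliability and completeness of outcome measures. It sets none for compliance or diary return.

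**The concern.** The definition has three components, and the content named for the instrument speaks to part of one of them. The clearest gap is frequency. It is the one component for which the article states a target, and a daily repetition total does not show whether that target was met. Repetitions are also hard to read on their own, because the same count can come from a lighter or a heavier variant and participants adjust the count themselves.

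The timing of collection adds to this. When a diary covering six months is returned once at the end, a participant lost to follow-up may take the whole record with them. If return is related to adherence, the compliance figure is biased, and the design gives no earlier partial record to check against.

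At stake is whether this study can tell a definitive trial how much of the programme participants did. That bears on the article's secondary aims of learning whether the programme can be delivered as planned and whether reliable data can be collected.

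**Working it through.** The article states no compliance figure, expected diary return or dropout rate, so there is no figure to reproduce. The check compares the definition with the diary, then bounds the two sources of uncertainty.

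**Step 1. Definition against recorded content**

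| Component of compliance | Target stated | What a daily repetition count shows |
|---|---|---|
| Frequency | Twice a day | Days with any exercise; not one session versus two |
| Dosage | Repetitions self-directed; load may change | Repetitions; not the variant or load |
| Timing | None beyond twice a day | Not recorded in the content named |

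**Step 2. What is lost on frequency**

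Inputs: two sessions a day (Exercise intervention); six months taken as 183 days. Assumptions: the advice applies for the whole diary period, and nobody does more than two sessions a day.

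- Sessions advised = 2 × 183 = 366 per participant.
- If repetitions are recorded on *d* days, sessions done lie between *d* and 2*d*, so the share of advised sessions lies between *d*/366 and 2*d*/366.
- With *d* = 183, the range is 183/366 = 50% to 366/366 = 100%.

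A complete, returned diary with an entry every day therefore leaves session adherence uncertain by a factor of two. The share of days exercised, *d*/183, is known exactly.

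**Step 3. What a single late return could cost**

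Inputs: 30 participants planned per arm (Sample size). The numbers returned (*m*) and compliant among returners (*k*) are assumptions. The observed proportion is *k*/*m*. The lowest possible value in the arm is *k*/30 (all unreturned diaries non-compliant) and the highest is (*k* + 30 − *m*)/30 (all compliant).

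| Returned *m* | Compliant *k* | Observed *k*/*m* | Lowest *k*/30 | Highest (*k* + 30 − *m*)/30 |
|---|---|---|---|---|
| 27 | 22 | 81% | 22/30 = 73% | 25/30 = 83% |
| 23 | 18 | 78% | 18/30 = 60% | 25/30 = 83% |
| 18 | 14 | 78% | 14/30 = 47% | 26/30 = 87% |
| 15 | 12 | 80% | 12/30 = 40% | 27/30 = 90% |

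The row with 23 returned is 0.75 × 30 = 22.5 rounded up. It borrows the 75% completeness threshold only as a reference point, since the article does not apply that threshold to the diary. The width of the range is (30 − *m*)/30, so it depends only on the return rate: 10 percentage points at 27 returned and 50 at 15.

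**The case against.** The strongest reply is that this is a condensed article. The diary form is not shown and the assessment schedule is a figure that is not reproduced, so the form may hold more than repetitions. That stands against any claim that the diary records nothing else. It does not remove the mismatch, because the article itself states both the definition and the content, and the two do not fit.

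Three stronger readings are tempting, and the document does not support them.

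- A reader might infer that compliance cannot be measured at all. Daily entries show the days exercised, repetitions are part of dosage, and twice a day supplies a denominator for frequency. The measure is partial, not absent.
- A reader might infer that returned diaries will come mainly from those who stayed in and kept exercising. The article does not say so. A participant who stopped can still post the diary, and the 7-day call may recover some, although the text speaks of forms and does not name the diary.
- A reader might put a single figure on the bias. For example, 60% return with 80% adherence in returners and 20% in the rest gives 0.6 × 0.8 + 0.4 × 0.2 = 56% against a reported 80%. The inputs are all chosen, and none is in the article.

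Two further points stand. No progression threshold rests on compliance and phase 2 is analysed descriptively, so the main feasibility decisions do not turn on this. The absence of imputation is explained by the aim of testing data collection, and a low diary return would itself be a finding.

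**Conclusion.** The point holds in a limited form. As described, the diary covers part of the compliance definition: it gives days exercised and repetitions, but not whether both advised sessions were done or which variant was used. For a participant with an entry every day, that leaves session adherence anywhere from 50% to 100%, assuming twice-daily advice throughout and at most two sessions a day.

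Separately, one return at 6 months creates a risk of selectively missing adherence data. On the assumed scenarios the possible range for the arm is 10 percentage points wide if 27 of 30 diaries return and 50 if 15 return. Which applies is unknown, because no return rate is stated. Neither the direction nor the size of any bias can be read from the document.

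The matter is worth correcting because compliance is a named feasibility outcome and a definitive trial may inherit the instrument. It does not undermine the study's stated thresholds.

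**What to change.** 1. Add two items to each diary day: the number of sessions done (0, 1 or 2) and a tick for the exercise variant. Keep the repetition count.
2. Split the diary. Collect the first part with the 3-month postal questionnaire, in the return envelope already supplied, and the second part at 6 months.
3. Report intervention-arm adherence as sessions done over sessions advised, and describe repetitions and variant alongside. Because repetitions are self-directed, they have no fixed target and should not be turned into a percentage.
4. Report the number of diaries not returned, with best- and worst-case bounds over everyone randomised to that arm. This needs no imputation.

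The cost is slightly more recording each day for six months, a reprinted diary and one more item in the 3-month mailing. Daily burden could itself lower return, so the additions should stay at a number and a tick. If the full diary form already records sessions and variant, the first change reduces to stating so in the protocol.

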### Sample size

A formal sample size calculation will not be performed since this is a feasibility study. We therefore envisage being able to recruit 30 participants into each treatment arm, and we consider that this will give a robust and useful amount of information [71]. Part of the feasibility study is to investigate the feasibility of recruitment. However, we envisage recruiting 60 participants in 13 months.

We will use the primary outcome measure, the global rating of change scale, to inform a sample size calculation for a definitive RCT.

### Randomisation

Patients who fulfil the inclusion and exclusion criteria, read and understood the patient information sheet and have given written consent to take part in the trial will be randomised to either the intervention or the control. A web-based randomisation service with secure password protected login using random variable block-size will be used.

Due to the nature of therapeutic studies, blinding of the participants and physiotherapists is not possible [72].

### Data collection methods

#### Phases 1 and 3

Interviews will be recorded with a digital recorder. The interviews will then be transcribed verbatim and analysed.

#### Phase 2

Baseline data will be captured prior to randomisation in the physiotherapy clinic. Follow-up assessments will be 3 and 6 months (by post with a stamped addressed envelope for return). Participants will be asked to post back their exercises diary at the 6-month follow-up.

### Planned data analysis

#### Phases 1 and 3

The qualitative components will follow a thematic analysis approach, as described by Braun and Clarke (2006) [73]. Line by line coding, leading to a thematic analysis (using an abductive research strategy), will be used. Following data familiarisation, initial codes will be generated and peer reviewed, by a member of the research group, to search for common themes. This will be carried out using the NVivo software (NVivo qualitative data analysis Software; QSR International Pty Ltd., Version 11, 2015). For phase 1, the analysis will assess the lived experience of PFP; for phase 3, the analysis will broadly assess acceptability and feasibility of study design, intervention and training package to physiotherapists.

#### Phase 2

The analysis will focus on descriptive statistics and confidence intervals for the variables we are obtaining. The characteristics of the participants will also be described using means, standard deviations and ranges for quantitative variables and counts and proportions for categorical variables.

As this is a feasibility study, we are testing our ability to collect data; therefore, no data imputation will be performed to account for any missing data.

Feasibility threshold will be set at 75% for recruitment. Feasibility threshold will be set at 75% to assess reliability and completeness of outcome measures. Data relating to timing of the return of outcome forms, department referral rate, recruitment rate and numbers lost to follow-up will be recorded. Acceptability and tolerability of the treatment intervention will be assessed through completeness of outcome measures and feedback from the phase 3 qualitative interviews.

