### Purpose

The primary aim is to establish the feasibility and acceptability of conducting a definitive RCT which will evaluate the clinical and cost-effectiveness of a loaded self-managed exercise programme for people with patellofemoral pain compared to usual physiotherapy.

Secondary aims include establishing: if the devised loaded self-managed exercise programme can be delivered as planned in an NHS physiotherapy outpatient clinic; if the outcome measures are feasible to use within an NHS setting; if reliable data can be collected; a sample size calculation for an RCT; if the intervention is acceptable and tolerable to participants and physiotherapists; if it is feasible to recruit and randomise participants; the potential barriers to recruitment and the training package delivered to physiotherapists.

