### Monitoring

The exercise intervention is low risk and is commonly used in the population. The occurrence of an adverse event as a result of participation within this study is not expected, and no adverse event data will be collected.

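### The only quantitative indicator named for acceptability and tolerability of the treatment is questionnaire completeness, which shows form return; the exercise diary already collected is not linked to that judgement.

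*Protocol article*

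**What the plan says.** The Purpose section puts acceptability in the primary aim of the study and lists as a secondary aim to establish "if the intervention is acceptable and tolerable to participants and physiotherapists". Planned data analysis, Phase 2, says how this will be judged: acceptability and "tolerability of the treatment intervention will be assessed through completeness of outcome measures", with feedback from the phase 3 interviews as the second source named in that sentence.

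The same paragraph uses completeness for another purpose: "Feasibility threshold will be set at 75% to assess reliability and completeness of outcome measures". Data collection methods shows what completeness depends on after baseline: "Follow-up assessments will be 3 and 6 months (by post with a stamped addressed envelope for return"). Outcome assessments adds a reminder: "Non-responders will be telephoned after 7 days to encourage them to complete the forms and return them".

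Two other statements bear on the point. Outcome assessments says "Feasibility outcomes of compliance levels will be monitored through a participant activity diary", filled in daily for 6 months with the number of repetitions done; Data collection methods has it posted back at the 6-month follow-up. Monitoring says "no adverse event data will be collected".

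**The concern.** Returning a questionnaire and tolerating a treatment are different things. A participant may give up the exercise in the first weeks and still return both follow-up forms. Another may follow the whole programme and return neither. The reminder call raises form return without changing what anyone does with the exercise.

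The difference matters in this trial. The intervention is done twice a day and to a degree that brings on the participant's pain, and the article itself recognises that adherence to exercise is often poor. How many participants keep going is therefore a main thing the definitive trial would need to know. With no adverse event data, tolerability has no direct quantitative measure elsewhere either. If completeness is read as acceptability, good form-chasing may pass for a tolerable programme, and poor postal return may count against a programme that participants liked.

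**Working it through.** The plan gives no figure to reproduce. The check has two parts: what each planned source can show, and how far completeness could track adherence.

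**1. Sources side by side**

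| Source | Where in the article | What it shows | Linked to acceptability? |
|---|---|---|---|
| Completeness of outcome measures | Planned data analysis | Whether forms come back filled in | Yes |
| Phase 3 interviews: 8–10 participants over both arms, 8–10 physiotherapists | Study design; Phase 3 interviews | Views, difficulties, barriers | Yes |
| Daily exercise diary, 6 months | Outcome assessments | Repetitions done, hence continuation | No; described as compliance |
| Numbers lost to follow-up | Planned data analysis | Who stopped supplying data | No |

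The one quantitative source that records what participants did is not among those named for the judgement.

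On the interviews: if the 8–10 participants were split evenly between arms (an assumption; no arm ratio is given), 4 to 5 would come from the intervention arm, that is 4/30 = 13% to 5/30 = 17%. They are chosen purposively, so even a larger share would not give an estimate of how often people stop.

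**2. Illustration of how weakly completeness may track adherence**

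Inputs from the article: 30 participants per arm (Sample size); 75% completeness level (Planned data analysis). Since 0.75 × 30 = 22.5, at least 23 of 30 must return forms. Applying the level to one arm is my choice for the illustration.

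Assumed inputs, not in the article: true adherence *a*; return probability *r*₁ in those who adhere and *r*₀ in those who do not.

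Overall return probability: *p* = *a*·*r*₁ + (1 − *a*)·*r*₀. Probability of meeting the level: P(X ≥ 23), with X ~ Binomial(30, *p*).

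Example: *a* = 0.40, *r*₁ = 0.90, *r*₀ = 0.80 gives *p* = 0.36 + 0.48 = 0.84 and P(X ≥ 23) = 0.91.

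| Return in adherers / non-adherers | *a* = 20% | *a* = 40% | *a* = 60% |
|---|---|---|---|
| 85% / 85% (unrelated) | 0.93 | 0.93 | 0.93 |
| 90% / 80% (mild link) | 0.84 | 0.91 | 0.95 |
| 95% / 60% (strong link) | 0.18 | 0.46 | 0.80 |

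Completeness separates a poorly followed from a well followed programme only if return depends strongly on adherence. At 40% adherence the level is met with probability 0.46 to 0.93 across these assumptions. Nothing in the article indicates a strong link, and reminder calls would tend to weaken one.

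**The case against.** The case on the other side has weight on five counts.

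- **The interviews are part of the same sentence.** They are a real second source. They sample responders and non-responders, seek out participants lost to follow-up, ask about difficulties with the exercise, and include the treating physiotherapists, whose view is part of the aim. It would be unfair to judge a qualitative sample by its coverage. This stands. What remains is that interviews do not yield a proportion.
- **Uptake is measured.** A reader might infer that the trial collects nothing on whether participants exercise. The article does not support that: the diary exists, and the general plan of descriptive statistics with confidence intervals for the variables obtained would naturally cover it. The gap is only that the diary is not connected to the acceptability judgement.
- **The diary may count as an outcome measure.** It is described in the section on outcome assessments. Even so, the sentence speaks of completeness. A complete diary is one that has been filled in, which is not the same as one showing that the exercise was done.
- **There is no decision rule here.** A reader might infer that the intervention goes forward if completeness reaches 75%, so that an untolerated programme would be declared acceptable. The article does not say so. Its 75% thresholds concern recruitment and the reliability and completeness of outcome measures. It states no pass mark for acceptability.
- **The probabilities rest on assumed rates.** They do. They show that the indicator can be insensitive; they do not predict what this trial will find.

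Nor is this detail that an article simply leaves to a fuller document: the article names the criterion, and the criterion named does not suit the aim.

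**Conclusion.** The point holds in a limited form. For a stated aim, the plan names a quantitative indicator that measures data return, and the same indicator already answers the separate question of data collection. The diary, which comes closer to what the aim asks, is collected but left out of the judgement. The interviews reduce the problem without removing it.

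The size cannot be fixed from the article. Under the assumed return rates, completeness meets the 75% level with the same probability, 0.93, at any adherence if return is unrelated to adherence, and discriminates well only if the link is strong. The conclusion does not depend on these rates. It rests on the wording of the acceptability sentence and on postal return with reminders being the route by which follow-up forms arrive.

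No claim is made that the plan contains a go-forward rule based on completeness, or that uptake goes unrecorded.

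**What to change.** Reword the acceptability sentence in Planned data analysis:

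- Use completeness of outcome measures for the data-collection aim only.
- Assess acceptability and tolerability in the intervention arm from diary-based adherence and from the proportion still exercising at 3 and 6 months, among all randomised to that arm, each with a 95% confidence interval.
- State the number of diaries not returned. Showing continuing, stopped and unknown as counts out of all randomised to the arm keeps to the plan's policy of no imputation and lets the reader see how much the missing diaries could matter.
- Report these figures beside the interview themes, which explain them.

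The cost is a change of wording, since the diary is already collected. The estimates will be imprecise: with 30 in the arm, 23 of 30 (77%) has a Wilson 95% interval of 59% to 88%. That is acceptable in a feasibility study if it is shown.

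A small drawback is that diaries come back only at 6 months and some will be missing, perhaps more often from those who stopped. One item on the existing 3- and 6-month forms, asking whether the participant has stopped the exercise and why, would be a useful low-cost addition. It goes beyond rewording and would need a change to the forms.
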